#### 4.4 Withdrawal criteria

Subjects may be withdrawn from the study at the discretion of the Investigator or Sponsor due to a safety concern or if judged non-compliant with trial procedures.

A subject must be withdrawn from treatment if the following applies:

1. Subject chooses to withdraw from the study at any time
2. Adverse Event requiring device explant
3. Pregnancy or intention of becoming pregnant

Reasons for withdrawals and discontinuation of any subject from the protocol have to be recorded.

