**Table 4. Summary of blood tests at each study visit**

| Blood test                                             | V1 | V3 | V5 | V6 | V7 | V8 | V9 | V10 | V11 | V12 | V13 | V14 | V15 |
|--------------------------------------------------------|----|----|----|----|----|----|----|-----|-----|-----|-----|-----|-----|
| Haematology (Full blood count)                         | x  | x  | x  | x  | x  | x  | x  | x   | x   | x   | x   | x   | x   |
| Routine Biochemistry (including Urea and Electrolytes) | x  | x  | x  | x  | x  | x  | x  | x   | x   | x   | x   | x   | x   |
| Liver Function test                                    | x  | x  | x  | x  | x  | x  | x  | x   | x   | x   | x   | x   | x   |
| Fasting glucose                                        | x  | x  | x  | x  | x  | x  | x  | x   | x   | x   | x   | x   | x   |
| Creatinine                                             | x  | x  | x  | x  | x  | x  | x  | x   | x   | x   | x   | x   | x   |
| HbA1C                                                  | x  |    | x  |    | x  | x  | x  | x   |     | x   | x   |     | x   |
| Lipids (cholesterol, HDL, LDL, triglycerides)          | x  | x  | x  | x  | x  | x  | x  | x   |     | x   | x   | x   | x   |
| C-Peptide                                              | x  |    |    |    |    |    |    |     |     |     |     |     |     |
| Insulin                                                | x  | x  | x  |    |    | x  |    | x   |     |     |     | x   |     |
| Vitamin D                                              | x  |    |    |    |    | x  |    | x   |     |     |     |     |     |
| Iron studies                                           | x  |    |    |    |    | x  |    | x   |     |     |     |     |     |
| Vitamin B12                                            | x  |    |    |    |    | x  |    | x   |     |     |     |     |     |
| Serum Folate                                           | x  |    |    |    |    | x  |    | x   |     |     |     |     |     |
| Free Thyroxine                                         | x  |    |    |    |    |    |    | x   |     |     |     |     | x   |
| TSH                                                    | x  |    |    |    |    |    |    | x   |     |     |     |     | x   |
| Cortisol (Sub-group 1 only)                            |    | x  |    |    |    | x  |    |     |     |     |     |     |     |

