## **7 EARLY DISCONTINUATION OF THE STUDY OR INDIVIDUAL SUBJECTS**

### **7.1 Early Discontinuation of the Study**

The sponsor and/or Ethics Committee and/or government agencies may also request to stop enrolment of additional subjects for the study or an individual site for any reason. If the study enrolment is ended before the planned completion, subjects with a device implanted will be evaluated to determine if it is acceptable to leave the device in place and continue to follow the Schedule of Events.

|                                                                                   |                                                                                                  |                                           |                                                             |                                                  |
|-----------------------------------------------------------------------------------|--------------------------------------------------------------------------------------------------|-------------------------------------------|-------------------------------------------------------------|--------------------------------------------------|
| [figure not shown] | Title:
EndoBarrier TM
Gastrointestinal Liner
Diabetes Trial | Protocol No:
Version 5.0 | Sponsor:
Imperial College
London | Date:
5th March 2018 |
|-----------------------------------------------------------------------------------|--------------------------------------------------------------------------------------------------|-------------------------------------------|-------------------------------------------------------------|--------------------------------------------------|

In case of early discontinuation of the study, the follow-up visit (Visit 12 at 15 months) assessments should be performed for each subject, as far as possible. Subjects that have the device removed before Month 3 will return for the End of Treatment/Month 12 (visit 11). Subjects that have the device removed after Month 3 will return for the End of Treatment/Month 12 (visit 11), Month 15 (visit 12), Month 18 (visit 13) and Month 24 (visit 15) post explant follow-up visits.

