## 7.2 Early Discontinuation of Individual Subjects

Subjects may discontinue study treatment (EndoBarrier) for the following reasons:

- At the request of the subject.
- If the investigator considers that a subject's health will be compromised due to adverse events or concomitant illness that develops after entering the study.

Any subjects who withdraw from the study that have the device implanted will have the device removed as soon as it can be arranged. Subjects that have the device removed before Month 3 will return for the End of Treatment/Months 12 (visit 11). Subjects that have the device removed after Month 3 will return for the End of Treatment/Month 12 (visit 11), Month 15 (visit 12), Month 18 (visit 13) and Month 24 (visit 15) post explant follow-up visits.

All subjects (including both control and device arm) who withdrew from the study early (either prior or after their treatment started – visit 4), and where no follow-up visit has been agreed or arranged as part of the previous protocol version (V4.1), will be contacted over the phone by the study team to ask for their permission (verbal consent documented by the study doctor using a specific form filed in the medical records) to perform a short telephone consultation at Month 24 (equivalent to visit 15). Data collected during this visit will include:

- HbA1 (provided through their last routine appointment at their GP)
- Body weight in kg
- Adverse events (section 6)
- Medical history/medication changes (section 5.5.4)

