Conservatively, it was estimated that 15% of patients in the control arm will achieve the target but believe this to be an overestimate. The Steno study  is the best quality randomised study (80 patients in each arm) into the effect of best medical therapy published to date and demonstrated over an average 7.8 years significant improvements in HbA1c amongst those having intensive medical therapy from 8.4+/- 1.6 to 7.7+/-1.2, but no change in HbA1c amongst those continuing with standard medical therapy. This study defines the very best that could realistically be achieved in the control arm, but expect there to be very little if any change in this group. The reporting of HbA1c as an outcome measure was not in accordance with the newly defined IDF criteria, but considering the small average reduction achieved in the Steno study, it will be assumed that a target of 15% of patients reaching the endpoint is a conservative estimate. Company data on the small number of patients who have reached a year with the device in place suggest that 40% will achieve this target.

According to our own experience with the device in the commercially sponsored study, up to 30% of patients in the treatment group may have the device removed early. Nevertheless other commercially sponsored (unpublished) studies of this device have achieved lower explant rates ([name] – GI Dynamics). We have therefore diluted the treatment effect from 40% vs. 15% to 35% vs. 15% achieving the target of 20% reduction in HbA1c for treatment arm vs. standard arm. 73 patients per group will give 80% power to detect a significant effect. Adding 10% loss of follow-up increases the sample size to 80 per group.

The dilution was calculated starting from the assumption that 40% of patients with the device will reach the target (this estimate is based on company data based on diabetic patients in the same range of BMI as in the present proposal). If 30% of patients in the treatment group need to remove the device early but remain available for follow-up, in the worst case scenario, the proportion reaching the target is the same as in the control group, bringing the estimate for the treatment group to 32.5%. However most of them will keep the device for some time, having some benefit, so it is plausible to assume that the estimate is higher than 32.5%.

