## 8.2 Data Analysis

Patient characteristics will be summarized. Summaries of continuous variables will be presented as means and standard deviations if normally distributed, and as medians and inter-quartile ranges for skewed data, whilst categorical variables will be presented as frequencies and percentages. The difference between the two study groups in the proportion of patients achieving substantial improvement in the metabolic syndrome both at 12 and 18 months will be analysed using logistic regression adjusting for the stratification variables (BMI groups and sites). Analysis of secondary outcomes will be conducted using standard statistical procedures applicable to categorical or continuous data as appropriate. For missing values we will explore the pattern and the extent of missingness and we will carry out an appropriate form of multiple imputation if required. The analysis will be performed according to the intention to treat principle. All statistical tests will be two-tailed with a 5% significance level.

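### The visits listed after early device removal include no HbA1c draw near month 12, and Section 7.2 does not say whether they replace the standard schedule

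*Protocol*

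**What the plan says.** Section 7.2 opens with reasons for stopping the device. It then has a sentence beginning "Any subjects who withdraw from the study that have the device implanted", which requires prompt removal. The visit list follows directly: "Subjects that have the device removed before Month 3 will return for the End of Treatment/Months 12 (visit 11"). For removal after Month 3 the list is visits 11, 12, 13 and 15.

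Section 7.1, on early stopping of the whole study, repeats the list but also asks that "the follow-up visit (Visit 12 at 15 months) assessments should be performed for each subject, as far as possible".

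The last part of 7.2 adds a Month 24 telephone call for people who left early with no follow-up visit arranged. It takes "HbA1 (provided through their last routine appointment at their GP").

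The table titled "Table 4. Summary of blood tests at each study visit" marks HbA1c at visits 1, 5, 7, 8, 9, 10, 12, 13 and 15. The cells for visits 3, 6, 11 and 14 are blank. Table 2 places visit 10 at 11.5 months, visit 11 at 12, visit 12 at 15 and visit 13 at 18.

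Sections 5.5.1 to 5.5.3 schedule diabetes and dietitian reviews for the device arm at visits 6, 7, 9, 11, 12, 13 and 15 and make no exception after removal.

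On analysis, Section 8.2 says that the outcome "both at 12 and 18 months will be analysed using logistic regression", by intention to treat, with multiple imputation if required. Section 8.1 builds its effect size on the case where "30% of patients in the treatment group need to remove the device early but remain available for follow-up".

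**The concern.** The primary endpoint is a 20% fall in HbA1c, so a patient without an HbA1c at the analysis time has no observed outcome. The rule in 7.2 applies only to people who had a device, so any resulting gap falls on one arm. It also falls on patients selected by an event after randomisation: removal for an adverse event, for illness or at their own request. Section 8.1 expects these patients to respond less often than those who keep the device.

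A statistical analysis plan can choose how to handle missing values. It cannot recover samples that the protocol did not ask sites to take. If sites treat the list as the schedule after removal, the intention-to-treat comparison rests on assumption for exactly the patients that 8.1 counts on following.

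**Working it through.** **1. The plan's own figures.** For 35% against 15%, two-sided 5%, 80% power, using the pooled-variance formula without continuity correction:

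n = [1.96 × √(2 × 0.25 × 0.75) + 0.842 × √(0.35 × 0.65 + 0.15 × 0.85)]² / 0.20² = 72.4, rounded up to 73 per group. This matches 8.1; power at 73 is 80.3%.

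The 35% comes from 8.1's dilution: 0.70 × 40% + 0.10 × (15% + 23% + 31%) = 28.0% + 6.9% = 34.9%. The 6.9 points come from explanted patients, so the design assumes that their outcomes are observed.

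**2. HbA1c draws still to come, Table 4 against the 7.2 list.**

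| Removal | Standard schedule | 7.2 list | Near month 12 | Month 18 |
|---|---|---|---|---|
| After visit 6 (month 1), before Month 3 | 7 (V7, V8, V9, V10, V12, V13, V15) | 0 (V11 has no HbA1c) | none | none |
| After visit 7 (month 3), before visit 8 | 6 | 3 (V12, V13, V15) | none | V13 |
| After visit 9, before visit 10 | 4 | 3 | none | V13 |
| After visit 10 | 3 | 3 | V10 already taken | V13 |

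Visit 10 is the decisive omission. Visits 6, 7 and 9, also missing from the list, would not supply a 12-month value.

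**3. Patients affected.** The ceiling is 0.30 × 80 = 24 device patients, reached if removal is at 8.1's upper rate and every removal precedes visit 10. Taking 20% and 10% as assumed rates gives 16 and 8. The allowance for loss to follow-up is a separate 0.10 × 80 = 8 per arm. The share removed before Month 3, who would also lack month 18, is not given, so it lies between 0 and 24.

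**4. What imputation would have.** For removal before Month 3, the latest study HbA1c is visit 5 (day 10) or, failing that, screening. For later removal before visit 10, month 15 is the next value.

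**5. Direction of bias.** Take the ceiling case and 8.1's rates. Leaving the explanted patients out gives 40% in the device arm, 5.1 points above 34.9%. Counting them as non-responders gives 0.70 × 40% = 28%, 6.9 points below. Two simple conventions move the estimate in opposite directions, and 8.2 commits to neither.

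**The case against.** The strongest reply is that 7.2 sets a minimum for leavers. The list follows a sentence about people who withdraw from the study, and it nowhere excludes other visits. Section 4.4 ("A subject must be withdrawn from treatment if the following applies") puts removal for an adverse event under withdrawal from treatment, and 8.1 keeps the 30% removal rate apart from the 10% loss. The Rescue Therapy text in 5.5.2 uses HbA1c above 7.0% as a trigger after removal, which presupposes that someone measures it. On this reading, patients who merely lose the device keep the standard schedule.

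That reading is possible, so a reader who infers a flat contradiction between 7.2 and Sections 5.5.1 to 5.5.3 goes too far: the text is ambiguous. But the reply does not remove the problem. The rule is worded for anyone whose device is removed, and leavers with no visit arranged have their own provision in the Month 24 call. Even a true leaver explanted before Month 3 who attends visit 11 gives no HbA1c there.

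Other stronger inferences also fail:

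- **That 24 patients will be missing.** This is a ceiling. Section 8.1 says up to 30% and cites lower rates elsewhere. Section 1.2 reports one removal before the end of a six-month study with 34 patients (whether per arm is unclear); 1/34 is about 3%, or roughly 2 of 80.
- **That the device effect will be inflated by 5.1 points.** This needs an analysis that drops explanted patients. Section 8.2 plans intention to treat and allows multiple imputation.
- **That sulfonylurea dosing is unmanaged after removal.** Section 5.5.2 sets triggers, HbA1c or three successive self-tests, and asks that changes be discussed with the coordinating diabetologist. A mandatory dose review at explant is not needed on this ground.
- **That the control-only mark at visit 11 in Table 2's diabetologist row supports the point.** It is a clerical slip; Sections 5.4, 5.5.1 and 5.5.2 agree that both arms are reviewed.

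**Conclusion.** The point stands in conditional form. Followed as written, the 7.2 list gives device patients explanted before visit 10 no HbA1c near month 12, and those explanted before Month 3 no listed HbA1c at month 18, while controls have both scheduled. The protocol does not say whether the list governs. The complete gap is in 7.2, because 7.1 asks for visit 12 assessments in everyone. The Month 24 call does not fill it: it reaches only some leavers, relies on a GP value and falls outside both analysis times.

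The size is 0 to 24 of 80 device patients. The upper end needs 30% removal, every removal before visit 10, and sites treating the list as the whole schedule. No direction of bias can be claimed from the protocol alone. For removal before Month 3, any imputation would rest on day-10 or screening HbA1c at best.

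**What to change.** In 7.1 and 7.2, state that explanted patients who agree stay on the standard schedule, including visit 10 for month 12 and visit 13 for month 18, and that the listed visits are a minimum for those who decline. Add HbA1c to the visit 11 blood sample for patients on that short list.

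This needs a protocol amendment. The standard visits and draws are already planned for the device arm, and blood is already taken at visit 11, so the only new item is one assay. Some explanted patients will still decline visits, so the gap will shrink but may not close.

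As a separate clerical correction, change the visit 11 diabetologist entry in Table 2 from control arm only to both arms.

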### 2.4 Primary Endpoints

- Reduction in HbA1c by 20%

|                                                                                   |                                                                             |                                    |                                               |                                            |
|-----------------------------------------------------------------------------------|-----------------------------------------------------------------------------|------------------------------------|-----------------------------------------------|--------------------------------------------|
| [figure not shown] | Title:
EndoBarrier TM
Gastrointestinal Liner
Diabetes Trial | Protocol No:
Version 5.0 | Sponsor:
Imperial College
London | Date:
5 th March 2018 |
|-----------------------------------------------------------------------------------|-----------------------------------------------------------------------------|------------------------------------|-----------------------------------------------|--------------------------------------------|

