### 3.2 Treatment regimens

**Table 1. Summary of treatment groups**

| Treatment Sequence         | Number of subjects * | Treatment Period
1 | Follow-up Period
2 |
|----------------------------|----------------------|-----------------------|-----------------------|
| 1 EndoBarrier Device       | 80                   | 12 months             | 12 months             |
| 2 Standard Medical therapy | 80                   | 12 months             | 12 months             |
| Total number of subjects   | 160                  |                       |                       |

\* Additional subjects may be randomised to allow for any randomised subject that has withdrawn prior to commencement of treatment at Visit 4.

|                                                                                   |                                                                                                |                                           |                                                             |                                                  |
|-----------------------------------------------------------------------------------|------------------------------------------------------------------------------------------------|-------------------------------------------|-------------------------------------------------------------|--------------------------------------------------|
| [figure not shown] | Title:
EndoBarrier™
Gastrointestinal Liner
Diabetes Trial | Protocol No:
Version 5.0 | Sponsor:
Imperial College
London | Date:
5th March 2018 |
|-----------------------------------------------------------------------------------|------------------------------------------------------------------------------------------------|-------------------------------------------|-------------------------------------------------------------|--------------------------------------------------|

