blocks provide sufficient randomisation such that any potential unbalancing would be minor and that final analysis would be unaffected. Any additional randomisation need to be discussed and agreed with the sponsor and the CI. All patients withdrawn post-visit 4, so after treatment start, are part of the initial drop out calculations as per protocol and will not be replaced. At no point, will the total number of patients starting treatment exceed 160 and the final analysis will not be affected.

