#### Appetite food hedonics and brain reward systems:

Comparison of brain activation during fMRI paradigms and outcomes from behavioural measures of food hedonics and questionnaires will be compared between groups using a 2x2 ANOVA design including group (control vs. Endobarrier) between subject factor, time (baseline vs. follow-up visit) within subject factor, and group x time interaction to identify differential effects between groups. For fMRI studies analysis will use region of interest analyses (e.g. for food pictures orbitofrontal cortex (OFC), amygdala, caudate, nucleus accumbens and anterior insula; for MID task nucleus accumbens, dorsal striatum and OFC; for Go-NoGo task pre-supplementary motor area). In addition whole brain analysis will be performed to compare groups using statistical thresholds of voxel-wise correction FDR  $P < 0.05$  and cluster-wise correction  $Z > 2.3$   $P < 0.05$ . In addition linear regression will be performed to measure the correlation of variables at baseline or during the intervention with primary outcomes at 1 year e.g. weight loss and decreases in HbA1c within each group, to generate predictive markers and generate mechanistic hypotheses.

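### The Month 24 telephone contact for withdrawn patients collects one GP HbA1c with no date window, which does not directly supply the 12- or 18-month primary outcome

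*Protocol*

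**What the plan says.** **Endpoint and analysis times.** Section 2.4 gives the primary endpoint as "Reduction in HbA1c by 20" per cent, without a time. Section 8.2 says that the difference between groups in the proportion with "improvement in the metabolic syndrome both at 12 and 18 months will be analysed using logistic regression". I read this as the primary responder analysis, because section 2.1 defines the metabolic objective by the 20% HbA1c reduction. The fMRI paragraph of section 8.2 correlates variables "with primary outcomes at 1 year e.g. weight loss and decreases in HbA1c within each group". No 24-month analysis of the responder endpoint is named. Section 8.2 also states: "The analysis will be performed according to the intention to treat principle". Multiple imputation is to be used if required.

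**Recovery of data.** Section 7.2 covers withdrawals in both arms, before or after visit 4, for whom nothing was arranged under version 4.1. They are asked for verbal consent to "perform a short telephone consultation at Month 24 (equivalent to visit 15"), which records "HbA1 (provided through their last routine appointment at their GP"), weight, adverse events, and changes in history and medication.

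**Return visits.** Under the same section, device patients explanted before Month 3 return at visit 11 only. Those explanted later return at visits 11, 12, 13 and 15.

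**Replacement.** The note to Table 1 reads: "Additional subjects may be randomised to allow for any randomised subject that has withdrawn prior to commencement of treatment at Visit 4". Section 8.1 adds: "At no point, will the total number of patients starting treatment exceed 160 and the final analysis will not be affected".

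**The concern.** The protocol makes the effort to reach patients who have left, but asks for an HbA1c that is not tied to either analysis time. A value taken close to the call would fall about 12 months after the first analysis time and 6 months after the second. An older value might fall near one of them by chance, but nothing requires it.

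The missing outcomes may depend on allocation. The trial is not blinded to the patient: section 5.2 tells patients their arm at visit 2, which Table 2 places four weeks before visit 4. Willingness to stay can therefore differ between the arms even before treatment starts. Imputation lets the analysis run, but it rests on assumptions about these patients that an observed value near 12 or 18 months would replace.

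An analysis plan cannot repair this afterwards, because what is asked of withdrawn patients is fixed in the protocol.

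**Working it through.** **1. Which withdrawals would have an HbA1c at an analysis time?** Table 4 schedules HbA1c at visits 1, 5, 7, 8, 9, 10 (11.5 months), 12 (15 months), 13 (18 months) and 15 (24 months). It schedules none at visit 11 (12 months). Combined with section 7.2:

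| Withdrawn group | Contact in section 7.2 | HbA1c near 12 months | HbA1c at 18 months |
|---|---|---|---|
| Device removed after Month 3 | Visits 11, 12, 13, 15 | None scheduled at visit 11; visit 10 is not a listed return visit | Yes, visit 13 |
| Device removed before Month 3 | Visit 11 | None scheduled | None |
| Control, or left before visit 4, nothing arranged under version 4.1 | Month 24 call | Only if the last GP value happens to fall there | Only if the last GP value happens to fall there |

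Every randomised patient has a screening HbA1c (visit 1), so a 20% reduction could be computed from any later dated value. What is lacking is a later value at the right time.

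**2. The plan's own sample size.** Inputs from sections 8.1 and 8.2: 35% against 15%, two-sided 5%, 80% power. With the pooled-variance formula,

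n = [1.960·√(2·0.25·0.75) + 0.842·√(0.35·0.65 + 0.15·0.85)]² / 0.20² = (1.200 + 0.501)² / 0.04, which rounds up to 73 per group (power 80.3%).

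This reproduces the stated 73. With 10% loss, 73/0.9 rounds up to 82, against 80 stated. That is a difference of 2 patients and has no bearing here.

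**3. Power if the outcome is missing and only complete cases count.** The protocol gives no number of withdrawals, so the share without an outcome is an assumption, shown over a range. At 80 per arm:

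- 10% missing (72 per arm): 79.8%
- 20% missing (64 per arm): 74.9%
- 30% missing (56 per arm): 69.1%

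Only the 10% comes from the protocol. It is the allowance already built into the sample size.

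**4. Extreme-case bounds at 10% loss (8 of 80 per arm).** Suppose 35% and 15% respond among those observed.

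- Least favourable: device 0.9·35% + 0 = 31.5%; control 0.9·15% + 10% = 23.5%; difference 8 points. Pooled proportion 27.5%, standard error √(2·0.275·0.725/80) = 0.0706, z = 1.13, p = 0.26.
- Most favourable: device 31.5% + 10% = 41.5%; control 0.9·15% = 13.5%; difference 28 points.

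These are limits, not forecasts. The lower one needs every missing control patient to respond and every missing device patient to fail.

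**The case against.** The call is a residual step, limited to withdrawals with nothing arranged under version 4.1, and it is not the whole follow-up plan. Patients explanted after Month 3 are due an HbA1c at Month 18. Month 24 is also a sensible time for the other items: it matches the end-of-trial visit, and weight, adverse events and medication changes serve secondary endpoints. All of this stands, and it narrows the point to the HbA1c request.

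A reader might go further and infer that the recovered data are of no use to the primary comparison. The documents do not support that. Section 8.2 plans multiple imputation if required, and a later HbA1c, weight and medication changes can all serve as auxiliary variables, alongside any HbA1c taken before withdrawal.

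A reader might also infer from the replacement rule, and from the sentence saying that the final analysis is unaffected, that the analysis will shrink to those who started treatment. That is not supported either. Section 8.2 states intention to treat, section 7.2 contacts people who left before visit 4, and nothing excludes them. The exact wording of the analysis set can sit in the analysis plan.

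Finally, the 8-to-28-point range would apply to any trial of this size with 10% loss and the same observed rates. It does not isolate the effect of the Month 24 timing, and the 10% loss is already allowed for. That objection is correct.

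**Conclusion.** The mismatch is real but limited. Followed as written, section 7.2 gives the patients who depend on the call one HbA1c with no required timing, while the intention-to-treat analysis needs values at 12 and 18 months. The return visits leave the 12-month value uncovered for explanted patients, and the 18-month value uncovered for those explanted before Month 3.

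The size cannot be fixed from the protocol, because the number of affected patients is not given. The 8 and 28 points are outer limits at the planned 10% loss, not an estimate of bias. The power figures at 20% and 30% missing rest on assumed rates.

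The conclusion rests on two readings: that the 12- and 18-month analysis in section 8.2 is the 20% HbA1c reduction, and that no other contact asks these patients for earlier values. The change is worth making because the contact is already planned and the missing outcomes may depend on a known allocation.

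**What to change.** In the same contact, request all dated GP HbA1c results from randomisation to Month 24, for every withdrawal in both arms who is contacted, including those who left before visit 4. In the intention-to-treat analysis, use the result nearest 12 months and the result nearest 18 months, within a window stated in advance. Three months either side is one option; since those two windows meet at Month 15, add a rule so that one value does not serve both times. Flag these results as coming from external laboratories, and run one sensitivity analysis without them.

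The cost is a small change to the telephone form and the verbal-consent wording, through the amendment route in section 11.3.2. The downsides are differences between laboratories and the likelihood that some patients have no GP value inside the window. Their outcomes would still have to be imputed. That GP records hold usable dated values is an assumption, which the protocol does not address.
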